##### Urine samples

Spot urine samples are collected and analysed for albumin to creatinine ratio using standard techniques.

#### Diet: Self monitoring, intake and eating behaviours

##### Diet checklist

Seven day diet checklists are completed by the participants for self monitoring, with assistance from the parent or guardian if required. The checklists were adapted from those used in previous studies [9].

##### Dietary 24 hour recall

Dietary intake is assessed using a methodology adapted from USDA five pass method as used in the 2007 Australian National Children's Nutrient and Physical Activity Survey [47]. In brief, at each time point (weeks 9, 12, 26, 38 and 52) food and beverage intake is measured using a three pass 24 hour dietary recall. To assist with estimation of portion sizes a food model book is provided with picture guides of common household measures and life size images, plates, bowls, glasses and amorphous dishes.

##### Eating behaviour

Eating behaviour is assessed by the Eating Pattern Inventory for Children [48].

##### Qualitative aspects of the diet

Qualitative aspects of the diet including, perceptions of cost, satiety, ease of compliance are assessed by a locally developed questionnaire. This questionnaire is completed by the parent or guardian.

#### Physical activity, sedentary behaviour and fitness

##### Physical activity and sedentary behaviour

The Children's Leisure Activities Study Survey (CLASS) is completed by the participant with assistance from the parent or guardian if required. CLASS assesses a range of physical activity and sedentary behaviours. CLASS has been validated for use among children, and used by adolescents aged 13-16 years in the Nepean Study [49]

##### Fitness

Assessment of aerobic fitness is performed using a Bruce treadmill protocol and breath by breath gas analysis. VO_2 _peak (maximal oxygen uptake) is expressed relative to body mass [50].

#### Metformin compliance

Metformin adherence is assessed by pill counts by the clinical trials pharmacist at CHW.

### Data analysis

Data analyses will be carried out according to a pre-established plan, with the primary analysis based on intention to treat and with statistical support from the Clinical Epidemiology Unit, CHW. Analysis will be undertaken blinded, at the end of each phase of intervention. Generalised linear models using a repeated measures option will be used to assess differences in continuous variables between baseline and follow up by treatment group after adjusting for baseline covariates if necessary [51]. Mixed models will also be used to investigate changes over time. The mixed models procedure will take into account within subject correlations and missing data points. A time by group interaction will be included to investigate whether rates of change of adiposity and other primary outcomes are significantly different between the two study groups. In addition, the proportions of young people who were successful in decreasing adiposity will be compared between groups and the result expressed as number-needed-to-treat.

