### Randomisation

Treatment allocation occurs centrally by minimisation [36] with the aid of computer software [37] at CHW. To adjust for potential confounding influences participants are randomised into dietary groups stratified by sex, pubertal stage, categorised by the study physician as either prepubertal or early puberty (Tanner stage 1 and 2) or pubertal (Tanner stage 3, 4 and 5), and BMI status (overweight or obese as defined by the International Obesity TaskForce [31]).

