### Sample size

The sample size is based on the primary outcome, change in whole body insulin sensitivity index (ISI) between baseline and one year, using means and standard deviations (SD) from our clinical data [38] and are consistent with published data [30]. To have an 80% chance of detecting a significant increase in whole body ISI over a one year period at the two sided 5% level, 43 young people are required in each intervention arm, assuming a clinically significant increase in whole body ISI of 0.8 and an SD of 1.3. The high SD allows for the variation of insulin sensitivity during puberty. To accommodate a 20% dropout rate we will need to recruit 54 in each intervention arm (108 in total). A 20% drop out rate is based on two Australian paediatric weight reduction trials, PEACH and HELPP, which reported a 12% and 18% [39] dropout rate at 12 months. In addition, based on our clinical experience, we anticipate a maximum of 2 or 3 participants may progress to type 2 diabetes. However, treatment for these participants is likely to be consistent with the study intervention.

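### Baseline adjustment is left conditional although allocation is minimised on sex, pubertal stage and BMI status; fixing these factors and baseline ISI in the primary model would gain precision at almost no cost

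*Protocol article*

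**What the plan says.** Under Randomisation, allocation is by minimisation, and "participants are randomised into dietary groups stratified by sex, pubertal stage, categorised by the study physician" into Tanner 1–2 or Tanner 3–5, and by BMI status (overweight or obese). The stated purpose is to deal with possible confounding.

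Under Sample size, the target is "change in whole body insulin sensitivity index (ISI) between baseline and one year", "assuming a clinically significant increase in whole body ISI of 0.8 and an SD of 1.3", tested "at the two sided 5% level" with 80% power, so that "43 young people are required in each intervention arm". The same section adds: "The high SD allows for the variation of insulin sensitivity during puberty".

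Under Data analysis, repeated-measures generalised linear models compare baseline with follow-up by group "after adjusting for baseline covariates if necessary". Mixed models with a time by group interaction are also planned. The section names no covariate and does not say what would make adjustment necessary. It does say that analyses follow a plan set up beforehand, which is not shown, and that they are done blinded. Outcome measures lists potential confounders, among them pubertal stage and adiposity, but also quantities that arise after randomisation, such as change in adiposity and dietary adherence. It does not turn the list into an adjustment set.

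**The concern.** The design and the analysis do not match. The protocol treats sex, pubertal stage and BMI status as important enough to force balance on them, and then makes their use in the model optional. When a prognostic factor is balanced by design but left out of the model, its variation no longer contributes to the difference between arms but still sits in the residual. The reported standard error is then larger than the true one, so intervals are too wide and the test rejects too rarely.

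A conditional rule also leaves the covariate set to be settled once data are in hand. If need were judged by observed imbalance, minimisation would make that trigger unlikely to fire for the very factors that belong in the model. Analyses are planned at the end of each phase, so the choice could be made more than once and differently each time.

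A separate gain is open for baseline ISI. Comparing change from baseline between arms uses the baseline value, but less efficiently than including it as a covariate.

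**Working it through.** **Inputs from the protocol (Sample size).** Difference 0.8, SD 1.3, two-sided 5% level, 80% power, 43 evaluable per arm, 20% dropout.

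**Inputs assumed, because the protocol gives neither.** R², the share of variance in the 12-month change explained by the three minimisation factors: 0.10, 0.25, 0.40. The correlation ρ between baseline and 12-month ISI: 0.3, 0.5, 0.7.

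**Step 1: reproduce the stated size.** n = 2 × (1.3/0.8)² × (1.960 + 0.842)² = 41.5, so 42 per arm by the normal approximation. The t-based solution is 42.4, so 43. Dropout: 43/0.80 = 53.75, so 54. The protocol's figures reproduce with no covariate adjustment.

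**Step 2: power at 43 per arm, no forced balance, no adjustment.** SE = 1.3 × √(2/43) = 0.2804, and 0.8/0.2804 = 2.853. Power = Φ(2.853 − 1.960) = Φ(0.893) = 0.814 (t-based 0.805).

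**Step 3: minimisation factors.** Take balance as near perfect.

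- Factors omitted: the true SE is 0.2804 × √(1 − R²), but the test still uses 0.2804. Power = Φ(0.893/√(1 − R²)); actual two-sided alpha = 2 × [1 − Φ(1.960/√(1 − R²))].
- Factors included: power = Φ(2.853/√(1 − R²) − 1.960).

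| Assumed R² | Actual alpha, omitted | Power, omitted | Power, included (normal) | Power, included (t) |
|---|---|---|---|---|
| 0.10 | 0.039 | Φ(0.942) = 0.827 | Φ(1.048) = 0.853 | 0.845 |
| 0.25 | 0.024 | Φ(1.032) = 0.849 | Φ(1.335) = 0.909 | 0.903 |
| 0.40 | 0.011 | Φ(1.153) = 0.876 | Φ(1.724) = 0.958 | 0.954 |

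Compared on the normal approximation throughout, the gain is about 3, 6 and 8 percentage points. The right comparator is the omitted column, not 0.814, because forced balance already helps the unadjusted test.

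**Step 4: baseline ISI as covariate, reading 1.3 as the SD of change.** With equal variances σ² at both visits, the variance of a change score is 2σ²(1 − ρ) and the residual variance after covariate adjustment is σ²(1 − ρ²). The ratio is (1 + ρ)/2. Power = Φ(2.853/√((1 + ρ)/2) − 1.960).

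| Assumed ρ | Variance ratio | Power (normal) | Power (t) |
|---|---|---|---|
| Change score | 1 | 0.814 | 0.805 |
| 0.3 | 0.65 | 0.943 | 0.938 |
| 0.5 | 0.75 | 0.909 | 0.903 |
| 0.7 | 0.85 | 0.872 | 0.864 |

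The gains in steps 3 and 4 cannot simply be added, because baseline ISI and the factors are likely to share information.

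**The case against.** The strongest defence is that this is a condensed article pointing to an analysis plan that is not shown, and that plan may well name the covariates. That stands as a limit. But the article is not silent on adjustment: it states a conditional rule. If the plan fixes the covariates, the published sentence misdescribes it and still needs correcting.

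Four stronger readings are tempting and are not supported:

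- *The trial is underpowered or its type I error is inflated.* Neither follows. The planned 80% assumes no adjustment and reproduces. Leaving out balanced factors makes the test conservative.
- *Baseline ISI is ignored.* It is not. The models compare baseline with follow-up and allow for within-subject correlation. The loss is only that of a change score against covariate adjustment.
- *The SD of 1.3 is a cross-sectional SD, so a change-score analysis may miss 80%.* The protocol uses it in a calculation for change over one year and does not say otherwise. Its source is not available here. That is a separate sample size question and should not carry this point.
- *Adjustment will be triggered by imbalance, or covariates will be picked to favour a diet.* The text does not define the trigger. Blinded analysis makes steering towards one diet harder, though it does not prevent several models being compared.

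It is also fair to object that nothing shows that two Tanner groups, sex and overweight or obese status explain as much as 25% or 40% of one-year change. The remark about puberty suggests that it is prognostic but does not measure how strongly. The upper rows of the step 3 table are illustrations, not forecasts.

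**Conclusion.** The point holds as a matter of precision and pre-specification, not of validity. Following the text as written can give an unadjusted primary comparison that does not reflect the way participants were allocated. Under the assumed R² of 0.10 to 0.40, omitting the minimisation factors costs about 3 to 8 points of power at 43 per arm. Under the assumed correlations of 0.3 to 0.7, and if 1.3 is the SD of change, not using baseline ISI as a covariate forgoes a rise from about 81% to between 86% and 94%. The direction of both effects rests on the factors and baseline ISI being prognostic; their size rests on R² and ρ, which the protocol does not give, and on near-perfect balance and equal variances. The promised 80% stands. The open covariate choice remains a real but limited risk, reduced by blinding and possibly by the plan that is not shown. The change is worth making because it is nearly free.

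**What to change.** Replace the conditional clause in Data analysis with: *The primary ISI model includes baseline ISI, sex, pubertal stage (Tanner 1–2 vs 3–5) and BMI status (overweight vs obese) as fixed covariates regardless of observed imbalance.* Report the unadjusted result as a sensitivity analysis. Follow-up ISI, or its change, should then be the response: if baseline stays in as one of the repeated responses, a main effect of a factor shifts all visits equally and does nothing for the time by group contrast.

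The cost is one sentence and about four degrees of freedom: with 43 per arm the residual falls from 2 × 43 − 2 = 84 to about 80, which is negligible for power. All four variables are already recorded at allocation or at baseline. If the separate analysis plan already fixes this set, the protocol text need only be brought into line with it.

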## Discussion

Clinical insulin resistance and prediabetes in the paediatric population are rapidly emerging clinical problems with serious health outcomes. With appropriate management these conditions are potentially reversible or at least their progression can be delayed. This research study is the first trial designed to provide definitive data on the effective dietary management for this cohort. This is crucial information to prevent metabolic complications, type 2 diabetes and early cardiovascular disease.

